## Abstract

**Background:**

Lung function is highly age-dependent as it decreases in varying degrees with age, even in healthy people. Decreased lung function results in less elastic lung tissue, reduced chest wall compliance, reduced area for gas exchange, and even a variety of chronic diseases. Traditional Chinese health exercise (TCHE) has three components: “breath regulation,” “body regulation,” and “heart regulation,” which play an important role in the improvement of lung function. However, which component has the most significant effect on lung functioning remains unclear. Therefore, depending on the modality of conditioning, TCHEs will be divided into three exercise intervention groups: breath regulation group, body regulation group, and heart regulation group, in order to explore the magnitude of the effect of the different modalities of conditioning on the improvement of lung function.

**Methods:**

The prospective, parallel, single-blind, randomized controlled trial will evaluate the effects of different conditioning methods of TCHE on lung function in middle-aged and elderly people. The study subjects are healthy middle-aged and elderly adults, who will be randomly divided into the “breath regulation group,” “body regulation group,” “heart regulation group,” and “control group.” The control group will receive health education. Health education and exercise intervention in the three intervention groups will be provided for 6 months, 5 times a week, with each session lasting 60 min. The outcomes of interest include changes in the pulmonary function tests measured at baseline and 3 and 6 months after the beginning of the intervention. The primary outcome is the forced vital capacity (FVC), while the secondary outcomes include forced expiratory volume in 1 s (FEV1), FVC/FEV1 ratio, vital capacity (VC), and maximal voluntary ventilation (MVV).

**Discussion:**

This study will assess the effects of different conditioning methods of TCHE on lung function in middle-aged and elderly people. The final findings of this study will validate the effectiveness and safety of TCHE on lung function interventions in middle-aged and elderly people.

**Trial registration:**

China Clinical Trial Registry ChiCTR2100052687. Registered on November 3, 2021

**Supplementary Information:**

The online version contains supplementary material available at 10.1186/s13063-021-05980-5.

## Background

Pulmonary function is highly age-dependent, with a slow decline starting at 20–30 years of age [1]. Decreased lung function results in the loss of lung tissue elasticity, reduced chest wall compliance, and reduced area for gas exchange [2]. Even in healthy people, lung function decreases with age [3]. When lung function declines too rapidly, the incidence of related diseases, such as respiratory and cardiovascular diseases, greatly increases [4]. Chronic obstructive pulmonary disease (COPD) is one of the most common diseases presenting with decreased pulmonary function, and the Global Burden of Disease Study 2015 estimated that approximately 174 million people suffer from COPD worldwide [5]. The rapid decline in lung function is also a significant predictor of death [6]. In 2015, COPD was ranked the third cause of age-standardized mortality in men and women globally, with approximately 3.2 million patients dying of the disease [7]. Middle-aged and older people with lower lung function have a faster rate of decline in cognitive abilities, such as memory and executive functions, than those with higher lung function [8]. Research shows that early exercise intervention and care for healthy older people can effectively reduce the incidence of chronic diseases and reduce health care costs [9]. Due to accelerated aging, the population of people aged > 65 in China was projected to reach 400 million by 2050, of which 150 million were above the age of 80 [10]. Therefore, it is very important to intervene in the early pulmonary function of middle-aged and elderly subjects.

Exercise greatly affects health status, and a lack of adequate exercise may cause systemic inflammation, cardiac dysfunction, and decreased lung function leading to most chronic diseases [11–13]. For most healthy adults, the benefits of exercise far outweigh the risks, and regular exercise is beneficial to improve and maintain the health of lung function [14]. For people with respiratory diseases, exercise training is regarded as the cornerstone of lung rehabilitation since it promotes disease rehabilitation, improves postoperative recovery, and prevents complications [13, 15]. Therefore, regular exercise is of great significance for both healthy individuals and those with respiratory diseases. However, the importance of exercise remains overlooked by some doctors and patients [16].

Traditional Chinese health exercise (TCHE) is an effective means of maintaining health and fitness and managing stress [17]. It regulates and enhances the functions of various parts of the human body through constant postural changes, breathing exercises, and mindfulness. It also presents characteristics of traditional Chinese medicine, including the application of meridians and acupoints and the regulation of qi, which increases its medical value [18]. TCHE plays important roles in the improvement and treatment of lung function, since these methods emphasize a close relationship between exercise and breathing. A number of studies have shown a significant improvement in the lung function of those who practice the TCHE [19–21]. Traditional lung rehabilitation therapy utilizes either physical or breathing exercise only. TCHEs combine these two types of exercise with mindfulness activities, which may have additional beneficial effects on lung function [22]. Different from and in contrast with traditional lung rehabilitation, which focuses on the rehabilitation treatment of patients after illness [15], TCHE focuses on disease prevention, a characteristic that reflects the preventive role of traditional Chinese medicine [18]. All TCHEs (such as Taijiquan, Baduanjin) include three types of regulation, namely “breath regulation,” “body regulation,” and “heart regulation,” all of which are indispensable and present in varying proportions across TCHE. Although previous studies have investigated the effects of TCHEs on lung function, no studies have explored the effects of each of these conditioning modalities on lung function separately. Therefore, depending on the modality of conditioning, the TCHEs will be divided into three exercise intervention groups: breath regulation group, body regulation group, and heart regulation group, in order to explore the magnitude of their effect on the improvement of lung function.

The purpose of this study is to analyze the effects of “breath regulation,” “body regulation,” and “heart regulation” on the improvement of lung function and to explore which modality is the most effective intervention for healthy middle-aged and older subjects.

## Methods

### Trial design

The prospective, parallel, single-blind, randomized controlled trial will evaluate the effects of different conditioning methods of TCHE on lung function in middle-aged and elderly people. It fulfills the requirements of the Standard Protocol Items: Recommendations for Interventional Trials (SPIRIT) checklist [23].

The subjects will be recruited from Mengcheng County, Anhui Province, China. A simple randomization will be used to divide them into a breath regulation group, body regulation group, heart regulation group, and control group in a 1:1:1:1 proportion. The subjects in the control group will receive health education only and maintain their previous lifestyle, and the three experimental groups will undergo exercise intervention (including warm-up, relaxation, and stretching) and health education for 6 months, 5 times a week, with each session lasting 60 min. The main and secondary results will be tested at baseline and at 3 and 6 months after the beginning of the intervention. An overview of the research program flow is presented in Fig. 1. The SPIRIT flow chart of the time points for enrolment, interventions, and assessments is shown in Fig. 2.

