### Sample size calculation

Considering the results of a previous study that used forced vital capacity (FVC) as the primary outcome index [24], the sample size was calculated by one-way ANOVA in Power Analysis and Sample Size version 15.0.5 (PASS 15.0.5 NCSS, LLC, USA). With a power of 80%, an alpha of 0.05, a standard deviation of 48, a standard deviation of the means of 8.16, and a dropout rate of 20%, we aim to recruit a minimum of 120 subjects per each of the four groups.

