### Randomization and blinding

After screening, interview, and evaluation of qualifications, the subjects who meet the inclusion criteria will be randomly divided into the breath regulation group, body regulation group, heart regulation group, and control group using a random number generator. The random list will be generated by an independent person using a computer to ensure the anonymity of the allocation.

The distribution order will be saved in sequential numbers in opaque and sealed-bound envelopes with aluminum foil inside to ensure that the envelopes are not visible in bright light. After the details of the subjects are written on the envelope, the envelope can be opened.

The lead investigator and data analyst will not participate in any intervention. The blind method will be used for the outcome assessor and data analyst to prevent the selective reporting of outcome variables. The subjects, coaches, researchers, and follow-up personnel will not be blinded, due to the particularity of sports intervention. The evaluators will not participate in the recruitment and distribution of subjects, and subjects, coaches, and researchers will be asked to refrain from discussing the intervention measures with the evaluators before the end of the experiment. In the event of serious side effects, blinding can be removed at the discretion of the outcome assessor.

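### Simple randomisation does not fit the stated minimum of 120 per arm: with the implied 480 subjects at least one arm will almost surely fall short, and age is left to chance

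*Protocol article*

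**What the plan says.** Under Trial design, "A simple randomization will be used to divide them into a breath regulation group" and three further arms, the last being the "control group in a 1:1:1:1 proportion". Under Randomization and blinding, subjects are allocated "using a random number generator", and "The random list will be generated by an independent person using a computer"; the sequence is kept in numbered, opaque, sealed envelopes. No section mentions blocks, strata or minimisation.

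Under Sample size calculation, "the sample size was calculated by one-way ANOVA". The inputs are 80% power, alpha 0.05, an SD of 48, 20% dropout and "a standard deviation of the means of 8.16". The result is that "we aim to recruit a minimum of 120 subjects per each of the four groups". No overall total is stated, and no rule for continuing recruitment until each arm is full.

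The Background says that pulmonary function depends strongly on age. The Eligibility criteria admit men and women aged 45 to 75. The Outcomes section speaks of changes from baseline. Statistical methods plans one-way ANOVA and covariance analysis between groups, without naming covariates.

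**The concern.** Simple randomisation allocates each subject independently with probability 1/4. Arm sizes are then random, and 1:1:1:1 describes their expectation only. A per-arm minimum that equals the expected arm size will therefore be missed by at least one arm almost every time. The article names a method and a size that do not fit together unless more than 480 subjects are enrolled or the list is in fact restricted. Neither is stated.

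Second, nothing in the design balances age, the one prognostic factor that the article itself emphasises. At stake are the credibility of the stated arm sizes, some precision, and either a visible departure from plan or unplanned extra recruitment.

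**Working it through.** **1. The plan's own figure.** Inputs from Sample size calculation: k = 4 arms, SD 48, SD of means 8.16, alpha 0.05, power 80%, dropout 20%.

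- Effect size f = 8.16/48 = 0.17.
- Noncentrality for the omnibus F test = 4n × 0.17² = 0.1156n.
- n = 95: noncentrality 10.98, power 79.9%. n = 96: noncentrality 11.10, power 80.3%. So 96 completers per arm are needed.
- 96/(1 − 0.20) = 120, as stated. Four arms give 480 by implication.

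**2. Arm sizes under simple randomisation of 480.** The sizes are multinomial (480; 1/4 each).

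- One arm: mean 120, SD = √(480 × 0.25 × 0.75) = 9.5, 95% range 102 to 139.
- All four arms can be at least 120 only if each is exactly 120: P = 480!/[(120!)⁴ × 4⁴⁸⁰] = 0.000096, or 0.01%.
- From 1,000,000 simulated allocations, the smallest arm has mean 108.8, median 110 and 5th percentile 99. The gap between largest and smallest arm has median 22 and 95th percentile 40.

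**3. Total needed to meet the floor by simple randomisation.** Simulated chance that every arm reaches 120: 76% with 540 enrolled, 91% with 560, 95% with 570. That is about 570 − 480 = 90 extra subjects.

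**4. Effect on power.** Total completers are held at 480 × 0.8 = 384 and the SD of means at 8.16. Four patterns of means were tried: one arm apart, two against two, two extremes with two in the middle, and equally spaced.

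| Completers | Mean power | 5th percentile across patterns |
|---|---|---|
| Balanced, 96 per arm | 80.3% | – |
| Simple randomisation, each arm loses exactly 20% | about 80.2% | 76% to 80% |
| 384 completers split at random | 80.1% to 80.2% | 75% to 80% |

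The omnibus test depends mainly on the total, so a small arm is largely offset by larger ones.

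**5. Chance imbalance in age.** The article gives no age distribution. Assume it is uniform on 45 to 75, so the variance is 30²/12 = 75 and the SD 8.7 years.

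- With 120 per arm, the largest gap in mean age between any two of the four arms has median 1.6 years and 95th percentile 2.9 years.
- In an age-adjusted comparison of two equal arms whose mean ages differ by d, the variance rises by the factor 1 + (d/2)²/75. For d = 1.6 this is 1 + 0.64/75, or 0.9% more variance. For d = 2.9 it is 1 + 2.10/75, or 2.8% more.

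**The case against.** Several stronger readings are tempting, and the article does not support them.

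- *Simple randomisation cannot deliver the minimum.* The figure of 120 is a floor and no total is fixed. Recruiting until every arm reaches 120 is compatible with simple randomisation, and 1:1:1:1 is a valid statement of equal allocation probabilities. This stands, so the mismatch is not a strict contradiction. But no larger total or recruit-until rule is given, and the calculation ends at exactly 120.
- *The trial is underpowered because its smallest arm is short.* The power statement is for an omnibus test, and the mean loss is about 0.1 to 0.3 percentage points. This stands.
- *Imbalance biases the result.* A randomised comparison is not biased by chance imbalance. Analysing change from baseline removes stable differences in level, and covariance analysis is already planned. This stands; the cost is precision, and it is small. Unnamed covariates are detail that an article may leave to the analysis plan.
- *Sex drives FVC, so sex must be balanced.* The article says this of age only. If half the subjects are women (an assumption), some pair of arms would differ by 10 points or more in sex mix in about 45% of allocations. That is the largest of six pairwise gaps, and it does not make sex a documented prognostic factor.

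It can also be said that the computer list may already be restricted, and that simple randomisation is the least predictable scheme in a trial whose subjects, coaches and researchers are unblinded. The first possibility would make the word *simple* wrong. The second is a real advantage, but concealed, varying block sizes keep most of it.

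**Conclusion.** The concern holds as a mismatch between the stated method and the stated size. At the implied 480 subjects, the chance that all four arms reach 120 is 0.01%, the expected smallest arm is 109, and meeting the floor with 95% chance would take about 570. Leaving age unbalanced sits poorly with the article's own account of lung function.

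The importance is low to moderate. Mean omnibus power stays at about 80.1–80.2% against 80.3%, although in an unlucky allocation it can drop to about 75–76% for some patterns of means. Validity is not threatened. The case for change rests on internal consistency and low cost, and a reader should not infer that the trial is underpowered or biased. The arm-size figures assume 480 enrolled and unrestricted allocation; the age figures assume a uniform age distribution.

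**What to change.** Under Trial design and Randomization and blinding, replace simple randomisation with computer-generated permuted blocks, 1:1:1:1, with randomly varying block sizes in multiples of 4 (for example 4, 8 and 12) known only to the independent list generator. Stratify by age group, for example 45–59 and 60–75; these bands are illustrative. Sex is a sensible optional addition. Keep the independent list generator and the sealed envelopes, with one numbered set per stratum. Include the stratification factor in the planned covariance analysis. If the list is already restricted, correct the word *simple* and describe the restriction. If simple randomisation is kept on purpose, state the total, or the recruit-until rule, that secures 120 per arm.

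The cost is a new list and separate envelope sets, made before the first subject is randomised. No extra subjects are needed to reach 120 per arm with complete blocks and 480 enrolled. There are two downsides:

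- Allocations near the end of a block are somewhat more guessable in an unblinded trial. Concealed, varying block sizes limit this.
- Incomplete blocks can leave small shortfalls. An unfinished block of 12 can separate two arms by at most 12/4 = 3, so two age strata give a gap of at most 6, against a median of 22 under simple randomisation. Adding sex makes four strata and a gap of at most 12.

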**Fig. 1 Fig1:**
[figure not shown]
Flow chart of the research scheme

**Fig. 2 Fig2:**
[figure not shown]
SPIRIT figure. SPIRIT figure showing the times points for enrollment, interventions, and assessments. FVC, forced vital capacity; FEV1, forced expiratory volume in 1 s; MVV, maximal voluntary ventilation; VC, vital capacity

### Eligibility criteria

To facilitate the recruitment of subjects, exhibition stands will be set up at the Mengcheng Museum, Mengdie Square, Zhuangzi Community, and at the Second People’s Hospital of Mengcheng County, Anhui Province, and leaflets will be handed out. The conditions of each potential participant will be assessed through on-site enquiries and telephone interviews. Men and women who meet the following inclusion criteria will be eligible: (1) aged 45–75 years; (2) no history of respiratory diseases; (3) no previous practice of systematic TCHE, such as Taijiquan and Baduanjin; and (4) signed written agreement to participate voluntarily after fully understanding the research purpose and procedures. The exclusion criteria are as follows: (1) limited physical activity or other factors that hinder the performance of the exercise intervention, (2) current practice of other regular exercise regimens, (3) cognitive impairment, and (4) participation in other clinical studies.

### Sample size calculation

Considering the results of a previous study that used forced vital capacity (FVC) as the primary outcome index [24], the sample size was calculated by one-way ANOVA in Power Analysis and Sample Size version 15.0.5 (PASS 15.0.5 NCSS, LLC, USA). With a power of 80%, an alpha of 0.05, a standard deviation of 48, a standard deviation of the means of 8.16, and a dropout rate of 20%, we aim to recruit a minimum of 120 subjects per each of the four groups.

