### Statistical methods

The SPSS statistics software (IBM SPSS STATISTICS, 25.0 version, Armonk, NY) will be used for data analysis and statistical testing. The Kolmogorov-Smirnov test will be used to check whether the data conform to the normal distribution. The average ± standard deviation (SD) will be used to describe continuous variables, and categorical variables will be expressed as *n* (%). Paired sample *t*-test will be used for intra-group comparison, and one-way analysis of variance (ANOVA) and covariance analysis will be used for inter-group comparison. The homogeneity of variance will be tested before ANOVA followed by a comparison of between-group variability using the least significant difference method corrected for test level *α* using Bonferroni adjustment.

Covariance analysis will be used to control other non-interventional factors. Repeated measurement analysis of variance will be used to analyze the intervention effect at different intervention times. The statistical difference may be significant (if *P* < 0.05) and very significant (*P* < 0.01).

All missing data will be analyzed using intention-to-treat analysis. Multiple imputation will be used to fill missing completely at random and missing at random, and last-observation-carried-forward will be used to fill miss not at random data.

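### The 80% power covers only the overall four-group F test; the corrected pairwise comparisons that must show which modality works best have less, and the plan does not say so

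*Protocol article*

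**What the plan says.** - **Sample size.** Under Sample size calculation, the protocol article states that "the sample size was calculated by one-way ANOVA in Power Analysis and Sample Size version 15.0.5". The inputs are "With a power of 80%, an alpha of 0.05, a standard deviation of 48, a standard deviation of the means of 8.16", plus 20% dropout, giving at least 120 recruits in each of four groups. Neither a pairwise contrast nor a divided alpha enters the calculation.
- **Question.** The Background closes by giving the purpose as the analysis of the three modalities and "to explore which modality is the most effective intervention for healthy middle-aged and older subjects".
- **Test that answers it.** Under Statistical methods, the ANOVA is followed by group comparisons "using the least significant difference method corrected for test level" by Bonferroni. The number of comparisons is not given, and the text does not say that they depend on a significant F test.

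**The concern.** The sample size and the conclusions rest on different tests at different significance levels. A significant F test shows only that the four means are not all equal. It does not show which modality differs from control, or which is best. Those statements come from pairwise tests at a stricter level, for which no power is given.

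Two misreadings are then likely. The 80% may be taken as the chance of showing that a modality works or leads. A non-significant pair may be taken as evidence that two modalities are alike, although the test had little chance of separating them.

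**Working it through.** **Inputs.** From Sample size calculation: within-group SD 48, SD of the means 8.16, alpha 0.05, power 80%, dropout 20%, four groups. From Statistical methods: Bonferroni-corrected pairs. Assumptions: all six pairs are corrected (0.05/6 = 0.0083), and covariates bring no gain. The individual means behind 8.16 are not printed, so a range of patterns is shown.

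**1. The plan's own figure.** f = 8.16/48 = 0.17. With n = 96 per group the noncentrality is 4 × 96 × 0.17² = 11.10 on 3 and 380 degrees of freedom, and the noncentral F distribution gives 80.3% (79.9% at n = 95). Then 96/0.8 = 120. The stated number reproduces exactly with the SD of the means computed with divisor 4. The divisor-3 convention would give 159, so it was not the one used.

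**2. Gaps that 8.16 allows.** The squared deviations of the four means sum to 4 × 8.16² = 266.34.
- Two extremes, two means midway: gap²/2 = 266.34, gap 23.08. This is the largest gap possible for any pair.
- Evenly spaced: 5 × step² = 266.34, step 7.30, range 21.9.
- One arm against three equal arms: 0.75 × gap² = 266.34, gap 18.84.
- Two against two: gap² = 266.34, gap 16.32.

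**3. Pairwise power at 96 per group.** The standard error of a difference is 48 × √(2/96) = 6.93. At 0.05/6, 80% power needs a gap of about (2.638 + 0.842) × 6.93 = 24.1, which is above 23.08. The third column of the table uses the noncentral t with 380 degrees of freedom. The fourth comes from simulation of the procedure proposed under the fix.

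| Pattern and pair | Gap | Flat Bonferroni, 0.05/6 | F test at 0.05, then 0.05/3 |
|---|---|---|---|
| Maximum range, extremes | 23.08 | 75.1% | 78% |
| Evenly spaced, extremes | 21.9 | 69.4% | 74% |
| Evenly spaced, two apart | 14.6 | 29.4% | not computed |
| Evenly spaced, adjacent | 7.30 | 5.6% | not computed |
| One arm against three equal | 18.84 | 52.8% | 61% |
| Two against two | 16.32 | 38.5% | 47% |

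For 80% at 0.05/6, the maximum-range pair needs 106 evaluable (133 recruited) per group. One arm against three equal arms needs 159 (199).

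**4. Naming a best modality.** One modality has its largest equal lead over the other two when control sits at the mean of the three. Then (2/3) × lead² = 266.34, so the lead is 19.99. Power per comparison at 96 per group is 59% at 0.05/6 and 68% at 0.05/3. By simulation, the chance of beating both at 0.05/6 is about 43%. It is about 36% when one modality differs from three equal groups, and about 4% with even spacing.

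**5. Sensitivity to the assumptions.** With three corrected comparisons, the maximum-range pair reaches 82% and one arm against three equal arms 62%. With six pairs and no dropout (n = 120), these become 86% and 65%. For the lead of 19.99 with no dropout, power per comparison is 72% at 0.05/6 and 79% at 0.05/3.

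**The case against.** The sample size section is not wrong. It names one-way ANOVA as its basis, and the number reproduces. Powering the global test and treating pairs as follow-up is a recognised design, and the aim is worded as exploration. This stands as far as it goes: a reader might infer that the sample size is miscalculated, and it is not. But the Discussion wants the comparison to guide exercise prescriptions, so the pairwise results will carry the message.

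A reader might also infer that no corrected pair can reach 80% under any reading. The protocol does not support that:
- The number of comparisons is not stated, and with three the most favourable pair reaches 82%.
- With no dropout and six pairs it reaches 86%. Imputation is planned, but it does not restore all the lost information, so this is an upper limit.
- Covariance analysis is planned. If 48 is an unadjusted SD, covariates explaining 1 − 96/106, or about 9%, of the variance would bring the maximum-range pair to 80%. One arm against three equal arms would need 1 − 96/159, or about 40%. No correlation is given, so the gain cannot be credited or ruled out.

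A third tempting step is to set a detectable gap of about 24 against the 150 mL tolerance given for FVC. That does not work. No unit is printed for 48 and 8.16, and 150 mL limits the spread of one person's two best efforts, not a difference between group means.

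Finally, Bonferroni is a valid correction. Replacing it is an improvement, not the repair of an error.

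**Conclusion.** The point holds as a gap between what is powered and what will be concluded, and it should be fixed. The 80% is correct for the F test. With six corrected pairs, 96 evaluable per group and no covariate gain, pairwise power is at most about 75%, and much lower in other patterns that fit the same planning values.

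The result for the trial's own question is firmer. Separating the best modality from both others stays below 80% per comparison at 0.05/6 and at 0.05/3, even with no dropout (there only just below, 79%, at 0.05/3), and beating both is harder than beating one. This conclusion depends on 8.16 and 48 being the right planning values and, like the other figures, takes no credit for covariates.

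**What to change.** 1. **Statistical methods.** Replace flat Bonferroni with the F test at 0.05 and, only if it is significant, each of the six pairs at 0.05/3. Once the four means are not all equal, at most three pairs can be truly equal, so the family-wise error stays at or below 0.05 (Shaffer's argument; simulation agrees). Power rises from 53% to 61%, 38% to 47%, 69% to 74% and 75% to 78% in the patterns tabulated. The price is that no pair can be declared different when the F test is not significant.
2. **Sample size calculation.** State that 80% applies to the F test only. Add the pairwise power of the procedure actually adopted: about 78% at best and 61% for one arm against three equal arms under item 1. Give the assumptions (96 evaluable per group, no covariate gain, pattern of means) and the unit of 48 and 8.16. The 75% and 53% belong to flat Bonferroni and should not be printed beside the new procedure.
3. **Conclusions.** Call a modality most effective only if it beats both other modalities. Otherwise report ranked estimates with confidence intervals, and do not read a non-significant pair as no difference.

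All three are changes of wording and need no extra participants. They do not bring the best-modality comparison to 80%: even at 0.05/3 it cannot exceed 68% at 96 per group. That is why item 3 is needed.
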